### Statistical Analysis

Plasma exosomes as well as exosomal protein and RNA concentrations will be described by their mean (SD) and their median (with extent). Comparison of baseline concentrations of participants with localized disease versus metastatic disease will be performed using nonparametric Wilcoxon tests. Comparison of pretreatment and posttreatment (surgical or drug) concentrations will be performed using nonparametric tests for matched data. Analyses will be carried out by subgroup (metastatic and localized) and on the whole population. Relative exosome variation before and after treatment will be compared in responders and nonresponders using nonparametric Wilcoxon tests. A Bonferroni correction will be applied to the *P* value to adjust the significance threshold during multiple comparisons.

The area under the receiver operating characteristic curve (AUC) modeling the response to treatment in function of initial exosome concentration will be plotted. AUCs with 95% CI values will be provided. The model will be adjusted to the type of disease (localized or metastatic). An exosome concentration threshold, predictive of response to treatment, will be determined. Performance (ie, sensitivity, specificity, and predictive values) associated with this threshold will be calculated. A similar approach will be followed concerning exosome concentration after treatment and delta between initial and posttreatment values. Different protein and RNA-derived markers will be analyzed. Performance associated to the absence or presence of these markers to predict response to treatment will be determined for each of the markers. Analyses will be performed under the software SAS 9.4 (SAS Institute).

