### Sample Size

A total of 30 patients, for whom all samples required for the study have been collected, should be included, distributed as follows:

Group 1: 15 patients with localized disease, for whom the 4 samples required for the study were collected.Group 2: 15 patients with metastatic disease, for whom the 3 samples required for the study were collected.

These numbers will provide preliminary data before considering a larger study. The primary objective of this study is to measure the markers of interest in patients. Given that the study focuses on rare cancers and that statistical analyses are only secondary objectives, no statistical power calculation has been performed for this study. Patients for whom the total number of required samples was not achieved will be replaced.

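### The whole-population comparison of responders and nonresponders has no stratification by disease type, so a difference between stages can appear as a response signal

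*Protocol article*

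**What the plan says.** The protocol article, Statistical Analysis, first paragraph, plans rank tests. On analysis sets it says "Analyses will be carried out by subgroup (metastatic and localized) and on the whole population". The next sentence says "Relative exosome variation before and after treatment will be compared in responders and nonresponders using nonparametric Wilcoxon tests". No stratified form of the test and no stage term is named.

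The second paragraph of that section turns to the ROC model of response on initial exosome concentration and says "The model will be adjusted to the type of disease (localized or metastatic)". It then extends the same kind of approach to the post-treatment concentration and to the change from baseline.

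Under Sample Size the cohorts are fixed: "Group 1: 15 patients with localized disease, for whom the 4 samples required for the study were collected" and "Group 2: 15 patients with metastatic disease, for whom the 3 samples required for the study were collected". Of power the section says "no statistical power calculation has been performed for this study", on the ground that "statistical analyses are only secondary objectives".

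Under Study Objectives and Endpoints, measurements bracket surgery in localized disease and first-line chemotherapy in metastatic disease. RECIST V1.1 is the response criterion, with no distinction between the cohorts.

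**The concern.** Disease type decides which treatment lies between the two measurements. Sampling times differ as well: 1 month and 6-8 months after surgery in one cohort, the third and sixth chemotherapy treatments in the other. It is therefore plausible that both the relative change in exosomes and the proportion called responders differ by stage. If both do, responders come mainly from one stage and nonresponders from the other, and an unstratified rank test partly compares stages.

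The authors treat stage as something to adjust for in the ROC model but name no such step for the rank test of change against response. The two analyses address the same secondary objective and could disagree for this reason alone. A positive pilot is meant to lead to a nationwide study, so a stage artefact could be carried forward as a candidate response marker.

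**Working it through.** **The plan's own figure.** 15 + 15 = 30 agrees with Sample Size. No alpha, effect size or power stands behind it, so there is nothing further to reproduce.

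**Inputs.** From the protocol: 15 patients per stage, and a two-sample Wilcoxon test on relative change. Assumed, because the protocol gives no figure: two-sided 5% level; normally distributed change with SD 1; a stage difference d in mean change of 0 to 1.5 SD; several pairs of response rates (localized/metastatic). Within each stage, change and response are independent, so every rejection is a false positive.

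**Mechanism.** The spurious shift between responders and nonresponders is approximately

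d × (localized share of responders − localized share of nonresponders).

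- 50/50: 7.5 of 15 responders and 7.5 of 15 nonresponders are localized. Shift = d × (0.50 − 0.50) = 0.
- 60/30: responders 9 + 4.5 = 13.5, localized share 0.67; nonresponders 6 + 10.5 = 16.5, localized share 0.36. Shift about 0.30 d.
- 80/20: responders 12 + 3 = 15, localized share 0.80; nonresponders 3 + 12 = 15, localized share 0.20. Shift 0.60 d.

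The shift vanishes if d = 0 or if the response rates are equal. Both differences are needed.

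**False-positive rate.** Simulation with 4,000 trials per row; Monte Carlo standard error about 0.003 near 0.05 and about 0.007 near 0.3.

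| d (SD) | Response rates (%) | Pooled Wilcoxon | Stratified (van Elteren) |
|---|---|---|---|
| 0 | 80/20 | 0.042 | 0.042 |
| 1.0 | 50/50 | 0.048 | 0.045 |
| 0.5 | 60/30 | 0.063 | 0.049 |
| 1.0 | 60/30 | 0.105 | 0.047 |
| 0.5 | 80/20 | 0.113 | 0.046 |
| 1.0 | 80/20 | 0.316 | 0.046 |
| 1.5 | 80/20 | 0.538 | 0.050 |

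A further simulated check at 1.0 SD with 80/20 puts the pooled rate a little lower, so it is quoted as about 30%. Over all 16 combinations examined, the stratified test stayed between 0.040 and 0.057.

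**Bonferroni.** The protocol applies this correction but does not state the number of comparisons. At an assumed 0.05/3 = 0.017, the pooled test at 1.0 SD with 80/20 still rejects in 0.171 of trials. A stricter threshold does not remove a bias.

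**Cost of stratifying.** A stage with no responders or no nonresponders contributes nothing to the stratified test. At 80/20 the chance per stage is about 0.8^15 = 0.035, so for at least one stage it is 1 − (1 − 0.035)² = 0.07. At 60/30 it is about 0.6^15 + 0.7^15 = 0.0005 + 0.0047 = 0.005. At 70/30 it is about 2 × 0.7^15 = 0.0095.

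**Pooled pre/post test.** With changes of −0.8 SD and +0.8 SD in the two cohorts, the pooled signed-rank test has power 0.012, while the cohort-specific tests have 0.78 and 0.80. With −0.8 SD in both, the pooled test has 0.98 against about 0.79 per cohort.

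**The case against.** **The same question has a stage-adjusted analysis.** The ROC approach, adjusted for disease type, is extended to the change from baseline. This stands, and it means the plan does not rest on the rank test alone. It does not make the pooled rank-test P value sound, and it shows that the authors already regard stage as worth adjusting for.

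**Stratification may be settled in the analysis plan.** That plan is not shown, and van Elteren is a form of the Wilcoxon test. In part this stands. But the protocol names adjustment for one analysis of response and not for the other, so as written a reader would run the ordinary test.

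**The size rests on assumed inputs.** This stands in full. The Results section expects concentrations and profiles to differ by stage; it does not say that relative change does, and no response rates are given. A reader might infer that the pooled responder test will produce false signals. The documents support only that it can, if both differences exist.

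**Coverage is unclear.** The sentence on subgroups and the whole population stands before the responder sentence and may not govern it. If it does, stage-specific responder tests are planned too. If it does not, the responder test is done on the whole population only and the exposure is greater.

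**The pooled pre/post test.** A reader might go further and infer that it is also invalid, that opposite changes in the two cohorts would be missed, and that it should be dropped. The documents do not support this. Cohort-specific tests are planned and would show opposite changes. The pooled paired test keeps its level when neither cohort changes, and it gains power when both move the same way. Cancellation affects how the pooled result is read, not whether the effects are found.

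**Conclusion.** The point holds for the whole-population responder comparison only. As written, that test has no protection against confounding by stage, in contrast to the adjusted ROC model beside it. With 15 patients per stage and no within-stage association, its false-positive rate at nominal 5% runs from about 5% (either stage difference absent) through about 6-11% (0.5-1.0 SD with 60/30) to about 30% (1.0 SD with 80/20) and about 53% (1.5 SD with 80/20).

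The range depends on assumed stage differences in both relative change and response rate, and on normally distributed change. The tests are secondary in a 30-patient pilot without a power calculation, so this is an inexpensive improvement and not a flaw that undermines the study.

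**What to change.** Add one sentence to Statistical Analysis (or to the analysis plan): on the whole population, relative change in responders and nonresponders will be compared with a Wilcoxon test stratified by disease type (van Elteren), in line with the adjustment of the ROC model, and stage-specific results will be reported beside it. This also settles whether the responder test is done by stage.

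Keep the pooled pre/post test, but present it only beside the two cohort-specific tests.

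The cost is wording; the stratified test is available in SAS 9.4 and needs no extra data or patients. The downside is that a stage with no responders or no nonresponders drops out of the stratified test: about 7% of trials at 80/20, 1% or less at 60/30 or 70/30. It grows if response is nearly uniform within a stage (at 90/20, 1 − (1 − 0.9^15)(1 − 0.8^15) = 1 − 0.794 × 0.965, or about 23%). Such a stage holds no within-stage information on response in any case, and the report should say so if it occurs.

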### Study Objectives and Endpoints

The main objective of this pilot study is to quantify exosomes from plasma and to analyze protein and RNA content in patients with sarcoma, with localized or metastatic disease. Analysis will be performed before and after surgery in localized disease and before and after first-line chemotherapy in metastatic sarcoma. Some patients may have received neoadjuvant chemotherapy with or without radiotherapy.

The secondary objectives are to:

Determine whether the initial exosome concentration, protein, and RNA profile vary in the plasma with localized or metastatic stage of the disease.Determine whether the exosome concentration as well as protein and RNA profile varies upon treatment.Determine whether the initial exosome concentration (T0) is associated with a response to treatment.Determine whether changes in exosome concentration before and after treatment are associated with a response to treatment.

The primary endpoint of the study is the quantification of exosome concentration in the blood, as well as the measurement of protein and RNA levels after exosome lysis. Measures will be performed before and after surgery in case of localized disease and before and after chemotherapy in case of metastatic disease.

The secondary endpoints will be exosome blood concentration, as well as protein and RNA concentrations measured after exosome lysis. Treatment response and tumor progression (locoregional or appearance of metastases) will be assessed by magnetic resonance imaging (MRI) or computed tomography (CT) scan using RECIST (Response Evaluation Criteria in Solid Tumors) V1.1 criteria.

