## Results

This study is expected to provide valuable insights into the role of exosomes in sarcomas, both in localized and metastatic stages. We anticipate that exosome concentration, as well as protein and RNA profiles, will differ between localized and metastatic disease, reflecting distinct tumor biology. Furthermore, we expect to observe variations in exosome concentration and content before and after treatment, potentially correlating with treatment response. A higher baseline exosome concentration may be associated with a poorer or more aggressive disease profile, while changes in exosome levels following treatment could serve as predictive biomarkers for therapeutic efficacy. The integration of exosome analysis with imaging-based assessments (MRI or CT scan using RECIST V1.1 criteria) will help establish correlations between exosome dynamics and tumor progression. If confirmed, these findings could pave the way for the use of exosomes as noninvasive biomarkers for monitoring sarcoma treatment response and disease progression, ultimately improving patient management.

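### In the 15 metastatic patients every planned response analysis uses a two-class outcome, so the graded tumor-size change behind RECIST 1.1 goes unused; a prespecified correlation should be added

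*Protocol article*

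**What the plan says.** All references are to the protocol article.

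- **Outcome.** Study Objectives and Endpoints has treatment response and tumor progression assessed on MRI or CT "using RECIST (Response Evaluation Criteria in Solid Tumors) V1.1 criteria". Progression there covers locoregional progression and new metastases. Data Collection lists imaging reports among the data gathered.
- **Analyses of response.** Statistical Analysis: "Relative exosome variation before and after treatment will be compared in responders and nonresponders using nonparametric Wilcoxon tests". For baseline concentration: "The area under the receiver operating characteristic curve (AUC) modeling the response to treatment in function of initial exosome concentration will be plotted". A concentration threshold with sensitivity, specificity and predictive values follows, and the same approach is applied to the posttreatment value and to the delta. Protein and RNA markers are assessed as present or absent for predicting response. Analyses are run in each subgroup and in the whole population, with a Bonferroni correction for an unstated number of comparisons.
- **Size.** Sample Size: "Group 2: 15 patients with metastatic disease, for whom the 3 samples required for the study were collected" and "Group 1: 15 patients with localized disease, for whom the 4 samples required for the study were collected". It adds that "no statistical power calculation has been performed for this study".
- **Expectation.** Results: combining exosome analysis with RECIST imaging "will help establish correlations between exosome dynamics and tumor progression".

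The article does not say which RECIST categories make a responder, and it gives no expected response rate.

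**The concern.** Each response analysis that the article names needs a yes/no outcome. None uses the percentage change in tumor size, or even the ordered RECIST categories, although a RECIST 1.1 assessment of measurable disease rests on measured lesion diameters. The marker is a concentration and the tumor change is a percentage. Reducing the second to two classes discards ordering within each class, and with 15 patients there is little to spare.

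Two things are at stake. A real relation between exosome change and tumor change in the metastatic cohort could well be missed. In addition, the pilot is meant to give preliminary data for a larger study, and the Discussion makes the nationwide study depend on positive pilot results. A correlation with its interval would be a more useful planning input than a comparison of, say, 2 patients with 13.

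**Working it through.** The plan has no power, event count or response rate to reproduce. The only input from the document is n = 15 metastatic patients. Response rate, number of responders k, true correlation and bivariate normality are assumptions.

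**1. How many responders?** Binomial, n = 15. At an assumed rate of 20%:

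P(0) = 0.8^15 = 0.035; P(1) = 15 × 0.2 × 0.8^14 = 0.132; P(2) = 105 × 0.04 × 0.8^13 = 0.231; sum = 0.398.

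| Assumed rate | Expected responders | P(none) | P(2 or fewer) |
|---|---|---|---|
| 10% | 1.5 | 21% | 82% |
| 20% | 3.0 | 4% | 40% |
| 30% | 4.5 | 0.5% | 13% |
| 50% | 7.5 | about 0% | 0.4% |

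**2. Smallest attainable P value.** For the exact two-sided Wilcoxon test it is 2 / C(15, k).

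- k = 1: 2/15 = 0.133, so significance at 5% is impossible.
- k = 2: 2/105 = 0.019. This exceeds 0.05/3 = 0.0167, so it fails once Bonferroni covers three or more comparisons.
- k = 3: 2/455 = 0.0044.

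**3. Power with a fixed number of responders.** Simulation, n = 15, two-sided 5%, no Bonferroni. Responders are the k patients with the greatest shrinkage. The responder test is the exact Wilcoxon on exosome change; the alternative is Spearman with percentage size change. True correlation 0.6:

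| Responders k | Wilcoxon | Spearman |
|---|---|---|
| 1 | 0% | about 62% |
| 2 | 20% | about 62% |
| 3 | 30% | about 62% |
| 4 | 32% | about 62% |
| 5 | 37% | about 62% |
| 7 | 37-39% | about 62% |

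**4. Power with the split left to chance.** Response is now cut at an assumed rate of 15 / 20 / 30 / 50%.

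| True correlation | Wilcoxon | Spearman |
|---|---|---|
| 0.5 | 16 / 19 / 25 / 29% | about 44% |
| 0.6 | 22 / 28 / 37 / 42% | about 63% |
| 0.7 | 30 / 41 / 52 / 58% | about 80% |

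With no true relation, the exact Wilcoxon rejects in 2.5 / 3.3 / 3.8 / 4.3% of runs and Spearman in about 5%. Part of the gap is therefore the coarseness of an exact test on few responders; most of it is lost information.

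**5. Limits of the correlation.** At correlation 0.6, Spearman power falls to about 50% with 12 measurable patients and 41% with 10. With all 15 and an illustrative Bonferroni level of 0.05/6 it is about 33%.

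**6. ROC analysis within the subgroup.** Hanley-McNeil interval for an assumed AUC A = 0.75, with k responders and m = 15 − k nonresponders: Q1 = A/(2 − A) = 0.600, Q2 = 2A²/(1 + A) = 0.643, A² = 0.5625.

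- k = 3, m = 12: variance = [0.1875 + 2(0.0375) + 11(0.0804)]/36 = 0.0318, SE 0.178, 95% CI 0.40 to 1.00 (upper limit truncated).
- k = 7, m = 8: variance = [0.1875 + 6(0.0375) + 7(0.0804)]/56 = 0.0174, SE 0.132, 95% CI 0.49 to 1.00.

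Even the most even split leaves 0.5 inside the interval.

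**The case against.** The strongest reply is that the plan fits its own objectives. They ask whether exosome concentration and its change are associated with response to treatment, and ROC curves, thresholds and predictive values need a two-class outcome. The correlations in Results are expected-findings prose about progression. The study is a pilot, its statistical analyses are secondary, and it openly waives a power calculation. The imaging reports are collected anyway, so a correlation could be added in an analysis plan that is not shown.

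Much of this stands. The planned analyses serve a stated objective and should stay, and the primary endpoint, quantification, is untouched. A reader might infer that the Results wording contradicts the analysis section. It does not strictly, because a group comparison can also address an association. The power waiver, however, does not answer the point, which asks for no further patients, only for use of a measurement already being taken.

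Three stronger readings are tempting and unsupported:

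- **That responders will certainly be very few.** The article gives neither a rate nor a definition. If stable disease counted as response, the split could be near even. The power loss remains in that case, but it is smaller.
- **That patients without measurable lesions are nonresponders whatever happens.** Complete response is not excluded, and the article gives no figure for how many such patients there would be.
- **That size change should replace the responder analysis.** Target-lesion change does not register a new metastasis, which the endpoint section counts as progression.

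The simulation also favors the correlation somewhat. It assumes a clean bivariate normal relation, full data and no Bonferroni, and it leaves out the planned whole-population analysis of 30.

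**Conclusion.** The concern holds as a matter of efficiency in the secondary analyses of the metastatic cohort. Every response analysis in the article is two-class, and the graded tumor-size change is not used. At an illustrative true correlation of 0.6, the responder comparison has from 0% power (1 responder) to about 40% (the most even splits), against about 62% for the correlation, or about 50% if 12 patients are measurable. The ordering is the same at correlations of 0.5 and 0.7 and at every response rate tried. The size rests on assumed correlations, bivariate normality and an unadjusted 5% level.

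The correlation would itself remain modestly powered. The point does not extend to the localized cohort, where size change after resection has no comparable meaning, and it does not show that the planned responder, ROC or threshold analyses are wrong.

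**What to change.** For cohort 2:

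1. Keep the planned responder, ROC and threshold analyses.
2. Add a prespecified Spearman correlation, with 95% CI, of (a) baseline exosome level and (b) its relative change with percentage change in the RECIST sum of target-lesion diameters, in patients with measurable lesions at baseline. Use the imaging matched to the sample, and name in advance which of the two on-treatment samples (third or sixth chemotherapy) is the main one.
3. Beside it, report exosome change by progression status, with new lesions counted as progression, so that new metastases and patients without measurable disease are not lost.

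The cost is one CRF field (sum of diameters at each imaging) and one more analysis, which should be counted in the Bonferroni correction or labeled exploratory. Patients without measurable lesions do not contribute to the correlation. No visit, sample or treatment changes.

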**Objective:**

This study aims to investigate whether sEVs can serve as reliable biomarkers for monitoring sarcoma progression and predicting recurrence risk.

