### Sampling

A total of 32 mL of blood (8× 4 mL EDTA [ethylenediaminetetraacetic acid] tubes) will be collected at each sampling for exosome analysis in both cohorts.

For cohort 1 (patients with localized sarcoma and undoing neoadjuvant chemotherapy), blood samples will be collected before surgery at cure 1 (sample 1) and at the last cure preceding surgery (sample 2). Then, at 1 month (sample 3) and 6-8 months post surgery (sample 4).For cohort 2 (patients with metastatic or locally advanced inoperable sarcoma), a blood sample will be collected before initial chemotherapy administration (sample 1). Then, at the third (sample 2) and at the sixth chemotherapy treatment (sample 3).Note that sample collection will take place before chemotherapy treatment even if the cure schedule is changed or postponed. Samples will be kept for a maximum of 2 hours at 4 °C.

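### Response is not defined for localized patients around surgery, and the pooled responder comparison is not stratified by stage, so it can be confounded by stage

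*Protocol article*

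**What the plan says.** Study Objectives and Endpoints gives one response criterion, RECIST 1.1, without a split by cohort: "Treatment response and tumor progression (locoregional or appearance of metastases) will be assessed by magnetic resonance imaging (MRI) or computed tomography (CT) scan". The same section sets the interval of interest by stage: "Analysis will be performed before and after surgery in localized disease and before and after first-line chemotherapy in metastatic sarcoma". It adds: "Some patients may have received neoadjuvant chemotherapy with or without radiotherapy".

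Sampling describes cohort 1 differently. There, localized patients are those having neoadjuvant chemotherapy, and "blood samples will be collected before surgery at cure 1 (sample 1) and at the last cure preceding surgery (sample 2"; samples 3 and 4 follow at 1 month and at 6-8 months after the operation. Sample Size requires all four samples from each of 15 localized patients and all three from each of 15 metastatic patients.

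Statistical Analysis counts surgery as a treatment alongside drugs and states: "Analyses will be carried out by subgroup (metastatic and localized) and on the whole population". The next sentence is the responder comparison: "Relative exosome variation before and after treatment will be compared in responders and nonresponders using nonparametric Wilcoxon tests". For the ROC analysis of response it says: "The model will be adjusted to the type of disease (localized or metastatic". It then plans a concentration threshold with sensitivity, specificity and predictive values, and the same approach for the post-treatment value and the change.

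The Abstract's objective is to find out whether the vesicles can be "reliable biomarkers for monitoring sarcoma progression and predicting recurrence risk". Recurrence is not named in the aim in the Introduction or in the four secondary objectives.

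**The concern.** Two of the four secondary objectives relate exosome level or change to treatment response. For metastatic patients on first-line chemotherapy, a RECIST response is a natural outcome. For localized patients it fits the neoadjuvant phase, when there is a tumor to measure. It does not fit the interval around surgery: after complete resection nothing is left to shrink.

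The analyst then has two options for a recurrence-free patient after surgery. The patient can be not evaluable, which empties much of the localized arm of the comparison. Or the patient can be called a responder, which makes being a responder largely a matter of being localized. Under the second option, an unstratified test on all 30 patients may pick up a difference between stages, or between surgery and chemotherapy, and report it as an association with response. Positive pilot results are meant to lead to a nationwide study, so a false signal of this kind has a cost.

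**Working it through.** **The plan's own figure.** The only figure to reproduce is the total: 15 + 15 = 30, which agrees. The article states that no power calculation was done, and it gives no effect size, SD or response rate.

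**Which interval can carry a RECIST response**
- Cohort 1, samples 1 to 2: tumor in place during neoadjuvant chemotherapy, so response can be assessed.
- Cohort 1, samples 3 and 4: after surgery. Assuming complete resection, imaging shows recurrence or none.
- Cohort 2, samples 1 to 3: tumor in place during first-line chemotherapy, so response can be assessed.

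The before/after interval named for localized disease (around surgery) is therefore the one in which response has no stated meaning.

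**How far response can align with stage.** Suppose, as an assumption, that 13 of 15 localized patients are recurrence-free and coded as responders, and 3 of 15 metastatic patients respond.
- Responders: 13 + 3 = 16, localized share 13/16 = 0.81.
- Nonresponders: 2 + 12 = 14, localized share 2/14 = 0.14.
- Difference: 0.81 - 0.14 = 0.67.

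If exosome change is unrelated to response within each stage, the expected mean difference between responders and nonresponders is 0.67 times the mean difference between stages. This describes means. The planned test uses ranks, so it was checked by simulation.

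**Simulation.** Inputs: 15 + 15 patients (Sample Size); normal marker; no association with response within either stage; 4000 runs per scenario (a few equal-rate runs dropped for having fewer than two responders); two-sided 0.05 per test. Responder rates and stage shifts are assumptions, shown over a range. The stratified test is van Elteren: within-stage rank sums, centered and weighted by 1/(N+1), added over stages.

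False-positive rate of the unstratified Wilcoxon test, by stage shift:

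| Responders, localized / metastatic | 0 SD | 0.5 SD | 1.0 SD | 1.5 SD | Stratified test, range |
|---|---|---|---|---|---|
| 100% / 10% | 0.049 | 0.209 | 0.618 | 0.918 | 0.019-0.021 |
| 100% / 20% | 0.048 | 0.174 | 0.534 | 0.833 | 0.032-0.040 |
| 100% / 30% | 0.048 | 0.143 | 0.435 | 0.727 | 0.038-0.046 |
| 80% / 20% | 0.045 | 0.107 | 0.311 | 0.520 | 0.046-0.048 |
| 50% / 20% | 0.044 | 0.060 | 0.104 | 0.178 | 0.048-0.056 |
| 20% / 20% | 0.039 | 0.043 | 0.045 | 0.043 | 0.043-0.046 |

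Two conditions must both hold for the error to rise: responder rates differ by stage, and the marker differs by stage. With either absent, the rate stays at or slightly below 0.05. In the 100% / 20% scenario the mean unadjusted AUC is 0.50, 0.62, 0.72 and 0.80 across the four shifts, so a single threshold taken from pooled data would look informative for the same reason. When every localized patient is a responder, the stratified test draws only on the metastatic patients.

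**The case against.** The strongest reply is that the plan already contains controls. Analyses by stage are planned, and the metastatic analysis cannot be confounded by stage. The ROC model is adjusted for disease type, and a similar approach is promised for the post-treatment value and the change, so both response objectives have a stage-adjusted analysis. This stands, and it confines the confounding to the pooled Wilcoxon test and to threshold performance if taken from pooled data. It does not remove it. The adjustment is stated for the ROC model only, and the AUC of a model containing stage also credits stage: in the 13/15 and 3/15 illustration, stage alone gives (13/16 + 12/14)/2 = 0.83.

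It can also be said that the whole-population sentence follows the pre/post comparison, so applying it to the responder test is an inference. That is fair. But the responder sentence names no cohort, and adjusting the response model for stage makes sense only if the stages are pooled.

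Responder categories may properly sit in the full protocol or analysis plan, so their absence here is no fault. The mismatch between the stated criterion and the surgical interval is in the text itself.

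A reader might infer that localized patients have no measurable tumor at all. Sampling rules that out: samples 1 and 2 precede surgery. A reader might also infer that the pooled analysis simply compares stages. That requires both conditions above, and the documents give neither responder rates nor the size of any stage difference. The Results section anticipates different concentrations and profiles by stage, but not a different relative change.

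Finally, the simulation applies no Bonferroni correction, because the number of comparisons is not given. A stricter threshold would lower the rates shown but would not remove the bias.

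**Conclusion.** The point holds as a conditional risk. One RECIST response is used for both cohorts, although it has no stated meaning for the interval around surgery, and the pooled responder test is not stratified by stage. Under assumed rates, and at a 1 SD stage shift, the false-positive rate runs from about 0.05 with equal responder rates, through 0.10 (50% vs 20%) and 0.31 (80% vs 20%), to 0.53 (100% vs 20%). Stratification keeps it at about 0.02 to 0.06 throughout.

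The documents do not support saying that the response objectives cannot be answered for localized disease or for the whole population: the neoadjuvant interval and the stage-adjusted ROC model are both available. Nor do they support saying that recurrence cannot be studied, since locoregional and metastatic progression is recorded by imaging. The recurrence issue is a mismatch of wording between the Abstract and the body. Severity is moderate: the primary objective of measuring the markers is untouched, and only secondary objectives of a pilot without a power calculation are affected.

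**What to change.** 1. State the outcome and the before/after interval for each cohort. Cohort 2: RECIST response to first-line chemotherapy. Cohort 1: RECIST change of the primary tumor over samples 1 to 2, with samples 3 and 4 related descriptively to recorded recurrence.
2. Make the by-cohort responder comparison the main one. If a whole-population test is kept, stratify it by stage (van Elteren), and report threshold sensitivity, specificity and predictive values by stage.
3. Reconcile Study Objectives and Endpoints with Sampling on which localized patients receive neoadjuvant chemotherapy. The first says some may have; the second defines the cohort by it, and Sample Size requires all four samples.
4. Align the Abstract's recurrence wording with the secondary objectives.

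The cost is wording, since imaging and progression data are already collected. The downside is that the main response results rest on 15 patients per cohort instead of 30. A formal time-to-recurrence analysis is not proposed: with 15 patients followed for about 6 months on average it would be barely estimable.
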